### Additional consent provisions for collection and use of participant data and biological specimens {26b}

Not applicable. Participant data will not be used in ancillary studies and no biological specimens will be required in the study.

## Interventions

### Explanation for the choice of comparators {6b}

Participants randomized to the control arm will receive TAU, which may include inpatient care delivered in the hospital or all other community CAMHS except ICCS. After the initial assessment, young people are treated with a combination of psychological, pharmacological, and/or social interventions as needed to achieve the goals set with their families. Treatment is not time-limited, but the average duration of treatment is about 50 days. Hospital treatment is followed by standard community treatment.

### Intervention description {11a}

Participants randomized to the intervention arm will receive ICCS, which provides intensive treatment for young people with severe mental illness in a community setting. This study defines ICCS as consisting of the following essential components:Small caseload: ICCS teams will have a service user/provider ratio of no more than 10:1.Team approach: ICCS providers will function as a team rather than as individual practitioners, and clinicians will know and work with all clients.ICCS team meeting: ICCS teams will meet frequently to plan and review services for each service user.Practicing team leader: The supervisor of front-line clinicians will provide direct services.Continuity of staffing: ICCS teams will aim to maintain the same staffing over time.Staff capacity: ICCS teams will operate at full staffing.Psychiatrist/psychiatric prescriber on staff: There will be at least one full-time psychiatrist per 100 service users assigned to work with the ICCS team.Nurse (RMN) on staff: There will be at least two full-time nurses (RMNs) assigned to work with a 100-client ICCS team.ICCS team size: ICCS teams will be of sufficient absolute size to consistently provide the necessary staffing diversity and coverage.Explicit admission criteria: ICCS teams will have a clearly identified mission to serve a particular population and will have and use measurable and operationally defined criteria to screen out inappropriate referrals.Intake rate: ICCS teams will take clients in at a low rate to maintain a stable service environment.Responsibility for hospital admissions: ICCS teams will be involved in hospital admissions.Community-based services: ICCS teams will work to monitor status and develop skills in the community rather than function as office-based teams.No dropout policy: ICCS teams will engage and retain service users at a mutually satisfactory level.Assertive engagement mechanisms: ICCS teams will use community outreach, motivational/engagement techniques, as well as legal mechanisms or other techniques to ensure ongoing engagement.Intensity of service: ICCS teams will provide a high amount of face-to-face service time as needed.Frequency of contact: ICCS teams will provide a high number of face-to-face service contacts as needed.Work with informal support system: With or without service users present, ICCS teams will provide support and skills for service users’ support networks, such as family, school, and extracurricular activities coordinators.Role of service users on treatment team: Service users will be involved in the functioning of the team (e.g. as members of interview panels).Provision of a day service: ICCS teams will provide a form of day service, such as a day school or partial hospitalization, to those service users who need it.

After the initial assessment, individualized goals are set with the family. Treatment includes a combination of psychological, pharmacological, and/or social interventions as needed to achieve these goals. Interventions can be delivered up to several times a day. Treatment is not time-limited, but the aim is to achieve the goals within 3 months of the initial assessment. ICCS is followed by standard community treatment.

### Criteria for discontinuing or modifying allocated interventions {11b}

Service user-clinician partnership will tailor interventions to service user needs and preferences as per the engagement approach. Participants have the right to withdraw from the study at any time, without giving a reason. If a participant decides to withdraw, they will be asked on the same day to provide a reason for withdrawal, but they are not required to do so. If a participant withdraws from the study, we will make every effort to report the reason for withdrawal as thoroughly as possible (e.g. adverse events, inability to adhere, inability to attend regularly for treatment or assessment). For participants randomized to the intervention arm, ICCS will be discontinued if they no longer wish to continue, or the trial is terminated at the request of the Data Monitoring Committee (DMC). Randomized participants who wish to withdraw from ICCS will be asked to confirm whether they are still willing to provide study-specific data at a 6-month follow-up and if they wish to participate in the nested qualitative study. It is also possible that the clinical team might withdraw the participant from ICCS if allocated. The reason for a clinician’s decision to withdraw a patient from the study must be recorded and the relevant clinician will clinically assess the participant and arrange appropriate care. Researchers at each site will make every effort to obtain all outcome measures, in priority order, from participants who drop out of treatment as soon as possible. Reasons for and dates of withdrawal from the study will be recorded on a withdrawal form, which will describe the circumstances of the withdrawal. Safety concerns identified through adverse events (AEs) and serious adverse events (SAEs) will be addressed through protocol amendments.

### Strategies to improve adherence to interventions {11c}

Participant compliance with ICCS attendance will be supported by offering compensation for travel expenses, providing research appointment reminders and gift vouchers at baseline and 6-month follow-up. Participating sites will receive a study manual and links to video-based training on the clinician-administered semi-structured interview, the Kiddie-Schedule for Affective Disorders and Schizophrenia for School-Age Children-Present and Lifetime Version (K-SADSPL), and on a web-based electronic data capture solution (MACRO EDC) and the randomization procedures. All teams will be invited to a bi-weekly Q&A session for study support. Monthly study update meetings will be held for Principal Investigators (PIs) and research assistants from all sites.

### Relevant concomitant care permitted or prohibited during the trial {11d}

Participation in other studies is not an exclusion but will be assessed by the research team for appropriateness, i.e. participation in a research trial of another intervention designed to provide community support.

### Provisions for post-trial care {30}

Participants will remain under the clinical care of the service they are being treated in, which will arrange further treatment or discharge from the service according to their local practices.

### Outcomes {12}

#### Primary outcome

The primary outcome is a time-to-event endpoint, as measured by the number of days from randomization to the first day of returning to or starting education, employment, or training (EET). For participants who do not return to or start EET, the time will be censored at the end of the follow-up period (6 months after randomization) or at the time of consent withdrawal. The time to return to or start EET, regardless of the duration of attendance, will be collected by contacting the relevant clinical team or the relevant EET establishments. If a participant attends more than one establishment on the same date, this will be counted as one attendance. EET opportunities for young people are important outcome measures for social and economic policy, but they are also vital upstream determinants of health [25]. Young people who spend more time not in education, employment, or training (NEET) are more likely to experience poor physical and mental health, unemployment, low-quality work, and lower incomes later in life [26].


#### Data collection

Primary outcome (days to attend EET) will be requested and collected from the relevant establishment at the end of the follow-up period (6 months after randomization) or at study withdrawal. Sociodemographic data and a clinical diagnosis (K-SADS-PL) will be collected from participants prior to randomization. All secondary outcome measures will be assessed at baseline and at 6 months (± 1 month) after randomization, except for the CA-SUS measure of service use, which will only be assessed at 6 months. In the 6 months following the day of randomization, blinded research assistants will contact the relevant clinical teams to find out the first day the participant returned to or started EET, and their attendance record will be collected from the relevant educational establishments or employers. The opportunity to participate in a one-on-one semi-structured interview will be offered to young people and healthcare professionals to explore their experiences with ICCS and TAU. Research teams will transfer non-identifiable data captured on paper case report forms (CRFs) to a password-protected MACRO database within one month. To minimize data loss, completed CRFs will be scanned or copied first, and stored at the research team’s base (NHS Trust or university). All participant information will be kept confidential, with names and addresses removed. Identifiable data (consent forms, email addresses) will be kept in locked filing cabinets, separate from other research data.

#### Participant timeline {13}

The participant timeline is shown in Table 2.

**Table 2 Tab2:**
[figure not shown]
Schedule of enrolment, intervention and assessments

*K-SADS-PL and CA-SUS can be completed within 2 weeks of randomization

#### Sample size {14}

The sample size calculation is based on Ougrin et al (2018) [23] which estimated the proportion of young people not in employment, education or training (NEET) at 6 months follow-up as 49% for the control arm (TAU) and 19% for the intervention arm, indicating a difference of 30% (95% CI from 13.1 to 47.3%). In line with the Adult IAPT targets of achieving 50% recovery versus baseline 30% recovery [27], a reduction of 20% or larger in the proportion of young people NEET is clinically significant and therefore the minimum clinically significant (proportion) difference (MCID) is set to 20% (49% NEET under TAU and 29% NEET under ICCS), which is at the lower end of the CI for the effect size. An adjustment of 5% for loss to follow-up was used based on the findings from Ougrin et al (2014) [14]. A sample size of 252 participants, with 126 participants per trial arm, is required to detect a 20% reduction in the proportion of young people NEET with 90% power using a two-sided log-rank test. The sample size for the semi-structured qualitative interviews is based on recommendations for deciding saturation in theory-based interview studies. At least 42 young people will be recruited, 21 with experience of ICCS and 21 with experience of inpatient care. In addition to the service users, we will interview 42 mental health professionals delivering both intensive community care and inpatient care to examine their experience of care and treatment delivery.

#### Recruitment {15}

Each NHS Trust involved in the IVY trial was chosen based on patient availability and clinical expertise, among other criteria. Clinical teams from each site will identify young people with psychiatric emergencies considered for inpatient admission within NHS CAMHS. Clinically stable, potentially eligible patients and their families will be approached by the research assistant. A comprehensible and full explanation of the study with the aid of an age-appropriate Participant Information Sheet (PIS) will be given to the patient and their families. Informed consent will be obtained from young people aged 16–18 years. Assent will be provided by young people aged 12–15 years along with parents’/guardians’ consent.

#### Internal pilot

A 12-month pilot will assess whether enough eligible patients can be recruited in 12 months to make a trial viable within the proposed 36-month main trial recruitment period. To progress, the trial must recruit 55 patients in total. Recruiting 60–80% (41–54) of the projected recruitment will trigger a discussion with the funder to remedy recruitment difficulties. Recruiting less than 60% (< 41) will indicate that the trial should not proceed. The overall schema for the trial is shown in Fig. 1.

## Assignment of interventions: allocation

### Sequence generation {16a}

Participants will be randomized on a one-to-one basis to the intervention arm or control arm via the web-based KCTU randomization system using a computer-generated allocation sequence based on variable block sizes with stratification per NHS Trust.

### Concealment mechanism {16b}

Relevant members of the study team from each participating site will receive training and access to the KCTU randomization system. Allocation will be concealed using this computer-generated mechanism. The unblinded members of the study team will have no role in the outcome assessment. All accessors (research assistants) collecting follow-up outcomes will be blinded to the treatment allocation of the participants. The senior statistician will be blinded and the second statistician unblinded. All randomizations will be recorded in an associated KCTU database.

### Implementation {16c}

The unblinded study team member will obtain a unique Participant Identification Number (PIN) from the MACRO eCRF system and enter it with the stratification data into the KCTU system to randomize the participant and subsequently will notify the participant and their clinical team of the group allocation.

## Assignment of interventions: blinding

### Who will be blinded {17a}

The research assistants from each study site responsible for outcome assessment, the senior statisticians and the senior health economist will be blinded to group allocation.

### Procedure for unblinding if needed {17b}

Not applicable. There will be no circumstances during the trial under which unblinding of the outcome accessors will be required.

## Data collection and management

### Plans for assessment and collection of outcomes {18a}

Data will be collected at specified time points (see Table 2) using pre-designed case report forms, via telephone or follow-up clinic visits depending on the participant’s stated preference.

### Plans to promote participant retention and complete follow-up {18b}

To minimize loss to follow-up, we will implement a multifaceted approach that includes encouraging patients to discuss any difficulties with attending ICCS appointments with their treating clinicians, financial assistance towards travel for research-related appointments, appointment reminders, and other evidence-based strategies, such as using incentives, sending greeting cards, personalizing letters, using colour printing, and keeping measures short and easy to complete.

### Data management {19}

KCTU will set up and maintain a web-based electronic data capture (EDC) system using the MACRO (InferMed) software. The EDC will be tailored for this project and data will be collected on bespoke CRFs. The system is GCP and 21 CFR Part 11 compliant with full audit trail and database lock functionality. Relevant staff at participating trusts will be trained to ensure reliable data capture using a standard eCRF proforma. Proforma data will be recorded anonymously and monitored for completeness, then collated and entered consistently into the MACRO database by a blinded researcher at each site. Variable ranges in the eCRF will be limited to reduce data entry errors. The blinded research assistant will enter data collected after informed consent, and the trial management team will monitor data completeness and accuracy. Research data will be entered and stored electronically whenever possible. Hard copies will be stored in locked filing cabinets at NHS sites. Electronic copies will be password-protected and stored on secure shared drives. Research data will be archived at sites and centrally for up to 10 years, then shredded, deleted, or destroyed. Audio recordings from the qualitative interviews will be uploaded to secure shared drives in anonymised and encrypted form and then deleted from portable devices within 24 h. Data will be stored confidentially and securely, with anonymised outcome data stored separately from personal information. All data will be password-protected and transferred securely using encrypted zip files in CSV, Stata, SAS, or SPSS format. Data will not be shared outside of the project team and hosting organizations.

### Confidentiality {27}

The project will adhere to GCP and data protection, security, and confidentiality legislation, including the Caldicott Report, ISO IEC 27002, the Data Protection Act, the NHS Trust’s research policy, the NHS Research Governance Framework, and HRA/REC approval processes. In accordance with the General Data Protection Regulation (GDPR) and Data Protection Act 2018, all stored electronic data will be deidentified and stored on password-protected secure servers, only accessible to authorized research team members.

### Plans for collection, laboratory evaluation and storage of biological specimens for genetic or molecular analysis in this trial/future use {33}

This is not applicable as no biological specimens will be collected.

## Statistical methods

### Statistical methods for primary and secondary outcomes {20a}

We will conduct intention-to-treat (ITT) analyses according to a pre-specified statistical analysis plan (SAP) approved by the senior statistician and trial steering committee before database lock. Participants who do not return to EET will be right censored at the end of the follow-up period (6 months after randomization) or when consent is withdrawn. A Cox proportional hazards model with NHS Trust as a random intercept and a trust-varying random coefficient of the treatment pathway will be used to compare the primary time-to-event outcome (time to return to EET) between the two trial arms. To quantify the effect size a hazard ratio and associated 95% CI will be estimated. For continuous secondary outcomes, mixed regression modelling will be used to compare continuous secondary outcomes at 6 months between trial arms, with NHS Trusts as random intercepts and trust-varying random coefficients of treatment pathway. Corresponding baseline values will be included as covariates in the models, if available. Distributional assumptions will be checked, and nonparametric approaches used where necessary. The CGI variables will be compared between trial arms using mixed models with inferences generated by robust methods to avoid relying on distributional assumptions for these limited scale variables (e.g. robust standard errors or cluster bootstrap). For CGI (measured at both baseline and 6 months), the analysis model will include baseline values and treatment pathway as fixed effects and NHS Trust random effects (random intercept as well as random coefficients for treatment pathway). For CGI-I (measured only at 6 months), models will not have a corresponding baseline value. Secondary outcomes measured as days on which an event happens over an observation period (e.g. time spent in hospital, number of days attending EET in the 6 months after randomization) will be compared between trial arms using a binomial distribution with a logit link and will allow for overdispersion. We will check whether the binomial distribution can be approximated by a Poisson model with overdispersion (i.e. negative binomial distribution, including an offset for the observation period). The models will contain the same terms as previous models, and the effect will be expressed as odds ratios (binomial distribution) or incidence rate ratios (Poisson model), depending on the distributional assumptions made. Binary outcomes from the Self-Harm Questionnaire will be analysed using mixed-effects logistic regression to compare the odds of participants reporting multiple (5 or more) episodes of self-harm between trial arms. Models will include baseline values and trial arm as fixed effects, and NHS Trust as a random intercept and random coefficient. Trial arm effect sizes will be reported with 95% confidence intervals (CIs). *P*-values will be presented, but there are no pre-specified significance thresholds for the (multiple) secondary outcomes.

The health economic analysis will use a within-trial, intention-to-treat approach with all randomized participants and taking the NHS/Personal Social Services perspective, including health and social care services provided with the education sector. As participants are in crisis at study entry (baseline), resource use data will be collected using a brief version of the CA-SUS focused on key health care resources, with a two-week window for completion. At 6-month follow-up, we will collect all-cause health and social care resources utilized by participants, excluding psychiatric inpatient, day-patient, and CAMHS services to avoid unblinding of research assessors. Instead, information on the use of these mental health services will be collected from clinical records at each site using a proforma to ensure accuracy and minimize unblinding.

Services will be costed using the most up-to-date nationally applicable unit costs [28]. Our primary economic analysis will be a cost-utility analysis using quality-adjusted life years (QALYs) derived from the CHU9D, with appropriate utility weights attached to health states [29] and QALYs calculated using the total area under the curve approach with linear interpolation between assessment points [30]. We will conduct a secondary cost-effectiveness analysis using the primary clinical outcome measure (time to EET). Costs and outcomes will be compared by trial arm, with mean values and standard deviations presented. Non-parametric bootstrap regressions will be used to obtain mean differences in costs and 95% confidence intervals, accounting for the non-normal distribution of economic data [31]. Cost-effectiveness will be assessed using the net benefit approach and standard methods [32]. A joint distribution of incremental mean costs and effects will be generated using bootstrapping to explore the probability of ICCS being the optimal choice compared to TAU, subject to a range of possible maximum values (ceiling ratio) that a decision-maker might be willing to pay for unit improvements in outcomes. Cost-effectiveness acceptability curves will be presented by plotting these probabilities for a range of possible values of the ceiling ratio [33]. These curves are a recommended decision-making approach for dealing with uncertainty in cost and effect estimates, and uncertainty regarding the maximum cost-effectiveness ratio that a decision-maker would consider acceptable. To provide more relevant treatment-effect estimates, all economic analyses will be adjusted for pre-specified variables of interest and baseline covariates, in line with the clinical analyses [34].

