## Methods: participants, interventions and outcomes

### Study setting {9}

Participants will be recruited at nine centres participating in the trial: South London and Maudsley NHS Foundation Trust, East London NHS Foundation Trust, North East London NHS Foundation Trust, Central and North West London NHS Foundation Trust, Oxford Health NHS Foundation Trust, NHS Lothian, Berkshire Healthcare NHS Foundation Trust, Cambridgeshire and Peterborough NHS Foundation Trust, and Cwm Taf Morgannwg University Health Board. All centres will run the trial in accordance with good clinical practice guidelines and will work in collaboration with NIHR local research networks and with the King’s Clinical Trials Unit (KCTU).

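### The 90% power assumes one common treatment effect across trusts, but the primary Cox model lets the effect vary over nine trusts; trust-level robust inference for CGI also needs a small-sample correction

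*Protocol article*

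**What the plan says.** Protocol article, Sample size {14}: "A sample size of 252 participants, with 126 participants per trial arm, is required to detect a 20% reduction" in the proportion NEET, "with 90% power using a two-sided log-rank test". The planning proportions are "49% NEET under TAU and 29% NEET under ICCS", and "An adjustment of 5% for loss to follow-up was used". No allowance for trusts or for between-trust variation in effect is mentioned. Alpha is not stated.

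Study setting {9}: "Participants will be recruited at nine centres participating in the trial". Sequence generation {16a} stratifies randomization by NHS Trust, so both arms occur within each trust.

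Statistical methods {20a}, primary outcome: "A Cox proportional hazards model with NHS Trust as a random intercept and a trust-varying random coefficient of the treatment pathway will be used". The same random intercept and random treatment coefficient recur in the secondary models. For CGI and CGI-I, mixed models are to be combined with robust inference, with "robust standard errors or cluster bootstrap" given as examples. The section promises 95% confidence intervals and sets no significance thresholds for secondary outcomes.

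The section on non-adherence and missing data {20c} accepts that delivery of TAU may differ from trust to trust.

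**The concern.** The trial was sized for one procedure and will be analysed with another. A log-rank calculation treats the hazard ratio as the same everywhere. A random treatment coefficient treats the nine trust-specific log hazard ratios as draws from a distribution and tests its mean. The uncertainty from having only nine draws does not shrink as more patients are added per trust. If effects do vary, the planned test has less power than stated, and the description of the trial as well powered in the Abstract carries an unstated condition.

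For CGI, sandwich standard errors and the cluster bootstrap rely on a large number of clusters. The comparison is made once, at 6 months, and trust is the only grouping in the models, so the natural cluster is the trust. Nine clusters are few, and without correction the intervals come out too narrow.

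**Working it through.** **Step 1: reproduce 252.** Inputs from Sample size {14}: NEET 49% and 29%, 5% loss, 90% power, two-sided. Assumption: alpha 0.05.

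- HR = ln(0.29)/ln(0.49) = 1.735; log HR = 0.551.
- Average event probability = (0.51 + 0.71)/2 = 0.61.
- Freedman events = [(1.735 + 1)/(1.735 − 1)]² × (1.960 + 1.282)² = 145.4, rounded up to 146.
- 146/0.61 = 239.3; 239.3/0.95 = 251.9, so 252.

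The match is exact. Alternatives do not match: Schoenfeld gives 240, and two proportions give 259 after loss (280 with continuity correction). So 252 is a plain log-rank figure with no trust term.

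**Step 2: add the trust-varying coefficient.** With nine trusts of similar size, Var(log HR) ≈ V + tau²/9. V was taken in two ways: 4/146 = 0.0274 (large-sample value for 146 events), or (0.551/3.242)² = 0.0289 (the value that makes power exactly 90% at tau = 0). Power = Φ(0.551/SE − 1.960). The tau values are assumptions.

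| tau | tau²/9 | Power, V = 0.0289 | Power, V = 0.0274 | Middle 95% of trust HRs |
|---|---|---|---|---|
| 0 | 0 | 90.0% | 91.5% | 1.74 |
| 0.1 | 0.0011 | 88.9% | 90.4% | 1.43–2.11 |
| 0.2 | 0.0044 | 85.5% | 87.1% | 1.17–2.57 |
| 0.3 | 0.0100 | 79.8% | 81.3% | 0.96–3.12 |
| 0.4 | 0.0178 | 72.3% | 73.7% | 0.79–3.80 |

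Worked line, tau = 0.3 and V = 0.0289: SE = √(0.0289 + 0.0100) = 0.197; 0.551/0.197 = 2.79; Φ(2.79 − 1.96) ≈ 0.80.

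**Step 3: check by simulation.** Nine trusts, about 240 evaluable participants, a trust-stratified Cox likelihood with a random log HR fitted by maximum likelihood, Wald z test, 600 runs per setting. Power at tau 0, 0.2 and 0.3 was 90.5%, 84.8% and 82.7% with equal trusts, and 88.5%, 82.7% and 81.8% with unequal trusts. With a t(8) critical value, power was about 81% even at tau = 0. The protocol does not state the reference distribution.

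**Step 4: CGI.** Assumption: robust inference is applied at trust level. For nine equal clusters, theory gives these type I error rates at nominal 5%:

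- uncorrected sandwich, normal reference: 10.2%
- sandwich with the G/(G − 1) correction, normal reference: 8.6%
- uncorrected sandwich, t(8): 6.1%
- corrected sandwich, t(8): 5.0%

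Simulation on a 1–7 scale (4,000 runs, equal and unequal trusts, with and without between-trust variation in effect) gave 10.5–11.4% for the uncorrected sandwich with z, 8.8–9.9% for the corrected sandwich with z, 11.0–11.8% for the percentile cluster bootstrap, and 4.8–6.0% for the corrected sandwich with t(8). Coverage is the complement: about 88–91% for the first three, about 94–95% for the last.

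**The case against.** **The power loss is conditional.** This stands. The documents give no between-trust SD and say only that TAU delivery may vary. A reader might infer that the planned model simply lacks 90% power; at tau 0–0.1 with a normal reference it has about 89–90%.

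**The model is defensible.** This stands too. ICCS is delivered by local teams, and TAU ranges from inpatient care to any community CAMHS other than ICCS. A reader might infer that a trust-stratified Cox model should become the primary analysis. But if effects vary, a model that ignores tau understates the standard error of the average effect. From the Step 2 formula with V = 0.0274, its type I error is 2 × [1 − Φ(1.96 × √(V/(V + tau²/9)))]: 6.9% at tau 0.2 and 12.7% at tau 0.4. Simulation gave 10.5% at tau 0.3, against 8.2% for the random-coefficient model with z. Fixed trust effects for CGI have the same weakness: 9.7% at 252 participants with a between-trust SD of 0.3 points. Both answer a question conditional on these trusts.

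**The CGI details may be in the SAP.** This partly stands. The methods are examples, the level of the robust standard errors is not stated, and the reference distribution and correction are left open. A reader might infer that the plan doubles the type I error for CGI; that follows only for uncorrected or bootstrap versions at trust level. Even so, both named methods under-cover at trust level with nine trusts unless corrected.

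**Early closure.** Trial status reports that recruitment stopped because the pilot progression criteria were not met. A reader might infer a final sample of about 54, too sparse for the model to converge. The document gives neither a final count nor any convergence failure. A zero variance estimate would simply reduce the model to a common effect.

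**Conclusion.** The stated power and the primary analysis do not correspond. The 90% at 252 holds for the planned model only if between-trust variation in the log hazard ratio is negligible. Otherwise power is about 86–87%, 80–81% and 72–74% at tau 0.2, 0.3 and 0.4, assuming alpha 0.05, nine trusts of similar size and a normal-reference Wald test. This is an unstated condition on the sample size, not an error in the Cox model.

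The CGI point rests on robust inference being applied at trust level. Then nominal 95% intervals cover about 88–91% without a small-sample correction and t reference. Because CGI is secondary and has no significance threshold, the consequence is intervals that are too narrow, not a wrong conclusion for the trial.

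**What to change.** 1. State beside the sample size that 90% power assumes a common treatment effect across trusts. Give the power of the planned model over a range of tau, such as 0 to 0.4, and name the reference distribution of the primary test.
2. Keep the random-coefficient Cox model as primary. Optionally add a Cox model stratified by trust as a sensitivity analysis, described as conditional on the participating trusts.
3. For CGI and CGI-I, specify that any trust-level robust inference uses small-sample-corrected cluster standard errors with t on 8 df. Do not use normal-reference sandwich errors or a percentile cluster bootstrap.

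Cost: a clarification to the protocol and, if it does not already say this, to the SAP before database lock; no new data are needed. The power statement becomes less favourable. CGI intervals widen by a factor of 2.306/1.960 = 1.18 against the corrected sandwich with z, or 1.18 × √(9/8) = 1.25 against the uncorrected one.
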